#### Secondary outcomes

2.6.2

(1)Quality of life will be assessed by a validated patient-reported outcome scale,^[18]^ which includes 27 items and assesses the impacts of hypertension on the 3 dimensions of quality of life, namely, the physical dimension (18 items), psychological dimension (4 items), and family-social dimension (5 items). Each item is divided into 5 categories, with each category receiving 0 to 4 points in sequence. A higher score indicates a worse quality of life. The total score equals the sum of the score of each item, ranging from 0 to 108 points. The detailed content of the scale is provided in the Supplemental Content (http://links.lww.com/MD/E870). We will also analyze the scores of individual dimensions separately.(2)Indicators related to diabetes mellitus, including changes in fasting blood glucose (mg/dl) and hemoglobin A1c (%), will be assessed.(3)Indicators related to dyslipidemia, including changes in total cholesterol (mg/dl), triglycerides (mg/dl), low-density lipoprotein cholesterol (mg/dl), and high-density lipoprotein cholesterol (mg/dl) levels, will be assessed.(4)Indicators related to hypertensive renal disease, including urinary albumin (g/l) and serum creatinine (μmol/l) levels, will be assessed.(5)Patient compliance will be determined. Patient compliance will be deemed poor if a patient administers heat-sensitive moxibustion fewer than 8 times per month. The proportion of patients with poor compliance will be assessed.

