### Interventions and co-interventions

2.5

Patients in the heat-sensitive moxibustion group will self-administer heat-sensitive moxibustion for one year while maintaining their original antihypertensive drugs. With the doctors’ help, the patients will first identify the heat-sensitive acupuncture points near CV8 (Shenque, the center of the navel), CV4 (Guanyuan, approximately 10 cm below the navel), and bilateral ST36 (Zusanli, approximately 7 cm below the lateral of the knee) and then perform moxibustion on the heat-sensitive acupoints. Self-sticking mini-moxa rolls will be used as the combustible material, which can be placed and burned in a moxibustion box (Fig. 2). A matching velvet bag can be used to wrap the moxibustion box to avoid burns. The suggested dose of moxibustion will be one moxa roll (approximately 30 minutes) per session, with 1 session per day and 7 sessions per week. Driven by a pragmatic design, we will allow the patients to adjust the dose of moxibustion to make it convenient, but they need to truthfully report the adjusted dose. Patients in the control group will only maintain their original antihypertensive drugs and will not perform heat-sensitive moxibustion. There will be no restriction on the type and dose of antihypertensive drugs, but other acupoint stimulation therapies, such as acupuncture, will be prohibited.

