#### Primary outcomes

2.6.1

(1)Changes in SBP and DBP (mm Hg) measured with an electronic sphygmomanometer. The average value of 3 measurements will be used.(2)Percentage changes in the dose of antihypertensive drugs. At each regular visit, the community doctors will determine whether the dose of antihypertensive drugs needs to be adjusted according to changes in blood pressure during the last month and will record the adjustment.

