### Study visits

2.8

During the 1-year follow-up period, the investigators will visit the patients monthly at the community health service centers, which are generally within 1 km of the patients’ homes. At month 0 (baseline visit), we will collect demographic characteristics (name, phone number, sex, age, education level, height, and weight) and disease-related characteristics (SBP, DBP, course of hypertension, comorbidities, smoking, drinking, and type and dosage of antihypertensive drugs currently used). At months 6 and 12, we will measure blood pressure, changes in doses of antihypertensive drugs, quality of life, blood and urine indicators, and AEs. The other regular visits (ie, months 1–5 and 7–11) will involve the distribution of moxa rolls and moxibustion boxes to patients, the assessment of patient compliance and the adjustment of the doses of antihypertensive drugs. A detailed schedule of the study visits is shown in Figure 2.

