### Statistical analysis plan

2.12

The analyses of the primary outcomes will be performed in the intention-to-treat population where either patients in the control group who performed heat-sensitive moxibustion or patients in the heat-sensitive moxibustion group who stopped moxibustion during follow-up will still be kept in their original group. Meanwhile, we will also perform sensitivity analyses using the perprotocol population to test the robustness of the main analysis. All analyses of the secondary outcomes will be performed in the per-protocol population. We will decide whether to impute missing data and which method should be used to impute missing data based on the actual distribution of the missing data.

For categorical or ordinal variables, we will calculate frequencies and percentages as the descriptive statistics and compare the between-group differences using the chi-square test or the linear-by-linear association test. We will present the means with standard deviations/errors and medians with interquartile ranges for continuous variables with normal and skewed distributions, respectively; the independent *t* test or the Mann-Whitney *U* test will be used to compare 2 groups. The effects of heat-sensitive moxibustion on the outcomes will be inferred using analysis of covariance or a logistic regression model adjusted for age, course of hypertension, baseline SBP, comorbidities, education level, smoking status, drinking status, and types of antihypertensive drugs recoded as dummies. The effects will be measured as the mean difference or odds ratio with a 95% confidence interval, and *P*-values will also be calculated. In addition, we will test 2 subgroup hypotheses:

(1)the dose of moxibustion: ≥3 sessions/wk vs <3 sessions/wk;(2)whether the heat-sensitive sensation appears: yes vs no.

The significance level indicating a difference between groups and subgroups will be α = 0.05. We will use R version 4.0.2 (The R Foundation for Statistical Computing, Austria) to run all statistical analyses.

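### The urinary marker of renal disease is fixed as albumin concentration (g/l), which varies with urine dilution, and serum creatinine is not adjusted for sex; an albumin-to-creatinine ratio and a filtration-rate estimate would cure both cheaply

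*Protocol article*

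**What the plan says.** Section 2.6.2, item (4), names "Indicators related to hypertensive renal disease, including urinary albumin (g/l) and serum creatinine", the latter in μmol/l. Both the indicators and their units are therefore fixed. The items on glucose and lipids in the same list are worded as changes; this one is worded as levels.

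Section 2.8 gives the timing: "At months 6 and 12, we will measure blood pressure, changes in doses of antihypertensive drugs, quality of life, blood and urine indicators, and AEs". No urine collection method is named in the text.

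On drug treatment, section 2.5 says "There will be no restriction on the type and dose of antihypertensive drugs". Section 2.6.1 has this rule for the regular visits: "the community doctors will determine whether the dose of antihypertensive drugs needs to be adjusted according to changes in blood pressure during the last month". Its second primary outcome is "Percentage changes in the dose of antihypertensive drugs". Section 2.4 lets patients choose their group.

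The adjusted model in section 2.12 includes age, course of hypertension and "baseline SBP, comorbidities, education level, smoking status, drinking status, and types of antihypertensive drugs recoded as dummies". Sex is recorded at month 0 (section 2.8) but is not in that list. Nor are change of drug dose during the study or any measure of urine concentration.

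**The concern.** A urinary albumin concentration mixes two quantities: how much albumin the kidney loses, which is the quantity of interest, and how much water it is dissolved in, which is not. Dilution varies within and between patients. At the least, this makes a true change harder to see.

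In a randomized trial, dilution would mostly be noise. Here the groups form by preference, drug treatment is free, and dose change is an outcome in its own right. If drug types or dose changes affect urine volume differently in the two groups, the albumin comparison moves without any difference in albumin excretion.

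Serum creatinine has a different weakness. Its level depends on sex as well as on renal function. With self-selected groups and no adjustment for sex, a difference in the sex mix shifts the comparison of levels.

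**Working it through.** The article gives no power, effect size or threshold for the renal outcome, so there is no stated figure to reproduce. The check covers the definition and what follows from it.

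**1. Effect of dilution within a patient.** Concentration = excretion / volume. Excretion is held at 30 mg/day (assumed; it cancels in the percentages). The volumes are also assumed.

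| Urine volume (l/day) | Albumin (g/l) | Relative to 1.5 l |
|---|---|---|
| 1.0 | 0.030 / 1.0 = 0.030 | +50% |
| 1.5 | 0.030 / 1.5 = 0.020 | 0% |
| 2.0 | 0.030 / 2.0 = 0.015 | -25% |
| 2.5 | 0.030 / 2.5 = 0.012 | -40% |

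These are shifts for one patient. They are not between-group effects.

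**2. Effect of a between-group volume difference.** Let one group have r times the urine volume of the other, with identical excretion. Its concentration is then 1/r of the other group's. The values of r are assumed.

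- r = 1.1: 1/1.1 = 0.909, so 9% lower
- r = 1.2: 1/1.2 = 0.833, so 17% lower
- r = 1.3: 1/1.3 = 0.769, so 23% lower

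**3. Chance of a significant difference if such a volume difference existed.** Section 2.11 plans 300 per group and allows 20% attrition: 300 x 0.8 = 240 per group. The standard deviation s of log concentration is assumed to be 0.8 to 1.2. The chance is approximately Phi(log r / (s x sqrt(2/240)) - 1.96). For r = 1.2 and s = 1.0: 0.182 / 0.0913 = 1.997; 1.997 - 1.96 = 0.037; Phi(0.037) = 0.515.

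| r | s = 0.8 | s = 1.0 | s = 1.2 |
|---|---|---|---|
| 1.1 | 26% | 18% | 14% |
| 1.2 | 70% | 52% | 38% |
| 1.3 | 95% | 82% | 67% |

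The nominal rate is 5%. Every entry depends on the assumed r. With r = 1 there is no inflation, only noise. Section 2.12 analyses secondary outcomes in the per-protocol population, so the numbers analysed may be below 240 per group.

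**4. Serum creatinine.** If mean creatinine differs by d between the sexes and the proportion of men differs by p between groups, the unadjusted comparison shifts by p x d with no difference in renal function. The document gives neither p nor d, so no size is claimed. Age is already in the model; sex is not.

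**The case against.** Item (4) has two indicators, and serum creatinine does not depend on urine dilution. This stands: the dilution problem belongs to the albumin indicator, not to the whole renal assessment.

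A reader might infer that the plan will produce a false renal benefit or harm through diuretic adjustment. The document does not support that. It never mentions diuretics, gives no share of users and shows no difference in urine volume. Both groups attend the same visits at the same centres, so it gives no reason to expect different sampling times. Drug-type dummies in the model absorb part of any confounding by drug class, though not dose changes during the study. The direction is also open. If moxibustion patients came to use less of a drug that raises urine volume, their urine would be more concentrated and the spurious result would be harm, not benefit.

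A comparison adjusted for baseline values would remove much of a stable difference in dilution or sex mix. The schedule figure is not available, so baseline urine and blood tests cannot be ruled out. But item (4) speaks of levels, and the only baseline outcome value in the covariate list is SBP. Adjustment would in any case not deal with a volume difference that arises during follow-up.

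Finally, an article condenses a fuller protocol. That covers the time of sampling and the choice of log scale, and neither is criticized here. It does not cover the unit g/l, which the article states.

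**Conclusion.** The point holds in a limited form. Fixing the urinary marker as a concentration makes it sensitive to dilution at unchanged albumin excretion. The noise is certain. The bias is plausible in a preference-assigned study with unrestricted drugs and dose change as a primary outcome, but it is not demonstrated. If group volumes differed by an assumed 10-30%, g/l would differ by about 9-23%. With an assumed log-SD of 0.8 to 1.2 and 240 per group, the chance of a significant difference would then run from 14% to 95%. All these sizes rest on assumed volumes and spread, none of which the document gives.

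Serum creatinine escapes dilution but is open to sex imbalance, because sex is recorded and not adjusted for. No size can be put on this from the document.

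This concerns one secondary outcome with no part in the sample size, so it is a worthwhile, inexpensive improvement and no threat to the main conclusions.

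**What to change.** In section 2.6.2, item (4):

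- Replace urinary albumin (g/l) by the urinary albumin-to-creatinine ratio from the same urine sample.
- Express serum creatinine as estimated glomerular filtration rate, calculated from the recorded age and sex. Alternatively, add sex to the covariates in section 2.12.
- Keep the raw albumin and creatinine values as supportive.

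The cost is one inexpensive urinary creatinine assay per urine sample already collected. The filtration rate is a calculation from data in hand, and the rest is wording. The ratio corrects for dilution only; it does not remove a true effect of drugs on albumin excretion, which remains a matter for the adjusted model. Time of sampling and scale of analysis can be left to the full plan.

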In 2017, the government of Xiashan District in Weifang city in Shandong Province tried for the first time to popularize heat-sensitive moxibustion as a daily health care method for all residents of the town. The measures taken to popularize the knowledge of heat-sensitive moxibustion included building a community center dedicated to providing free sessions of heat-sensitive moxibustion, organizing expert lectures, training patients on-site, and providing free moxibustion materials. After 2 years of efforts, the popularization work achieved satisfactory results – heat-sensitive moxibustion was practiced by 67% of the total population of 62,000 people. In addition, the per capita medical expenditure decreased by 49.8% and the number of annual outpatient consultations decreased by more than 16.7% compared with the values 2 years before.^[21]^ Unfortunately, no rigorous evidence was obtained regarding the effects of heat-sensitive moxibustion on hypertension with the exception of scattered case reports published during the popularization campaign. Learning from the successful experience in Shandong Province, the government of Jiangxi Province started to promote a public health project called “Everyone Uses Heat-sensitive Moxibustion, Everyone Enjoys Health” in several cities in 2019. Currently, the project is progressing smoothly. It could provide a favorable climate for the recruitment of participants and the successful completion of this study.

This study has potential limitations. The reduction of internal validity caused by the nonrandomized design is the main limitation. Although we have expanded the expected sample size as much as possible and will adjust for multiple confounders in the statistical analysis, the bias caused by unknown confounders cannot be completely avoided. However, the extrapolation of the results of this study, as a major advantage of a pragmatic study, will be enhanced. Another limitation is that it may be difficult for patients to remain compliant with the heat-sensitive moxibustion protocol for 1 year, and poor compliance will introduce bias. However, an important purpose of this study is to evaluate the feasibility of heat-sensitive moxibustion self-administration as a long-term intervention in patients in the community with hypertension. If compliance is poor, it will show that this is not a feasible strategy.

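### Compliance is analysed in the per-protocol population, so patients who stop moxibustion can leave the denominator of the measure meant to show whether the therapy was kept up for one year

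*Protocol article*

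**What the plan says.** - **Definition (2.6.2 Secondary outcomes).** "Patient compliance will be deemed poor if a patient administers heat-sensitive moxibustion fewer than 8 times per month". The summary is one figure: "The proportion of patients with poor compliance will be assessed". The section does not name the month or months to which it refers.
- **Therapy (2.5 Interventions and co-interventions).** Patients in the moxibustion group "will self-administer heat-sensitive moxibustion for one year while maintaining their original antihypertensive drugs". The suggested dose is one moxa roll per session, "with 1 session per day and 7 sessions per week", but "we will allow the patients to adjust the dose of moxibustion to make it convenient".
- **Population (2.12 Statistical analysis plan).** The primary outcomes use an intention-to-treat population that keeps patients who stopped moxibustion in their group. All secondary outcomes are assigned to the per-protocol population. Compliance is listed as secondary outcome (5), and no exception is made for it. The article does not define the per-protocol population.
- **Data collection (2.8 Study visits).** For months 1–5 and 7–11 the text lists "the assessment of patient compliance and the adjustment of the doses of antihypertensive drugs". Its list for months 6 and 12 does not mention compliance.
- **Use (3 Discussion).** Feasibility of long-term self-administration is called an important purpose of the study, and the authors add: "If compliance is poor, it will show that this is not a feasible strategy".

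**The concern.** Compliance is the outcome in which patients who stop are the events. A per-protocol population usually leaves out patients who did not follow the assigned treatment, and 2.12 describes keeping stoppers only for the intention-to-treat population. Applied as written, the rule can remove from the compliance denominator the very patients the measure should count.

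The single proportion adds to this. A monthly rule applied over a year produces a series of results per patient, and one figure without a time point cannot show whether use was sustained or faded. The statement at stake is about one-year feasibility, which the article presents as something the study will inform. The blood-pressure and drug-dose outcomes are not affected, because their main analysis keeps stoppers in their group.

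**Working it through.** The plan gives no compliance figure to reproduce. The check therefore covers the size of the denominator effect, the information lost in one proportion, and whether the data are collected.

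**1. Denominator effect.**
Inputs: 300 patients per group and a 20% attrition allowance (2.11 Sample size calculation). The 20% is an allowance for attrition, not a forecast of stopping moxibustion. It is borrowed here only to give a scale, and is halved and doubled to give a range.

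Let s be the share of the moxibustion group excluded because they stopped, and p the share below 8 sessions among those who remain.
- Reported in the per-protocol population: p
- In all who entered the group, with stoppers counted as below the threshold: s + (1 − s)p
- Understatement: s + (1 − s)p − p = s(1 − p)

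| s (assumed) | excluded / remaining of 300 | p (assumed) | reported | all who entered | gap |
|---|---|---|---|---|---|
| 10% | 30 / 270 | 0% | 0% | 30/300 = 10% | 10 points |
| 10% | 30 / 270 | 20% | 54/270 = 20% | 84/300 = 28% | 8 points |
| 20% | 60 / 240 | 0% | 0% | 60/300 = 20% | 20 points |
| 20% | 60 / 240 | 20% | 48/240 = 20% | 108/300 = 36% | 16 points |
| 40% | 120 / 180 | 0% | 0% | 120/300 = 40% | 40 points |
| 40% | 120 / 180 | 20% | 36/180 = 20% | 156/300 = 52% | 32 points |

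Whenever s is above zero and p is below 100%, the error runs one way: poor compliance is understated. If the per-protocol population were itself defined by the 8-session rule, p would be 0 by construction and the outcome would carry no information. If that population kept every stopper, s would be 0 and there would be no gap.

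**2. One proportion from a monthly rule.**
A patient who uses moxibustion daily for 4 months and then stops meets the rule in 4 of 12 months and fails it in 8. A patient who lapses only in month 5 fails it in 1 of 12. Both have months on each side of the threshold, and the article does not say how either enters the single proportion. Month-by-month reporting needs no such choice: the first patient is below the threshold from month 5 onwards, the second only in month 5. On persistence in months 10 to 12, the first fails and the second passes.

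**3. Data.**
The text of 2.8 lists compliance at 5 + 5 = 10 of the 12 monthly visits. Months 6 and 12 are not among them. Section 2.9 has patients hand back the previous month's box when they return for a visit, which suggests that use could be checked at those visits too. Figure 2, the visit schedule, is not shown and may settle this.

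**The case against.** **The article is condensed.** How monthly records are summarised for a descriptive secondary outcome is commonly left to a full protocol or analysis plan. That stands, and a missing aggregation rule would not be a finding on its own. The assignment of all secondary outcomes to the per-protocol population is different: the article states it outright, and it works against this outcome.

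**The per-protocol rule may be meant only for between-group comparisons, or may be defined so that stoppers stay in.** Either is possible. This is why the conclusion says that stoppers can, not will, leave the denominator. The wording still covers all secondary outcomes.

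**Compliance is the last-listed secondary outcome and concerns one arm.** True, and this limits the weight of the point. It nevertheless bears on a declared purpose of the study.

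A reader might also infer stronger points that the article does not support:
- *The 8-session cut is too low or contradicts the dose subgroup.* Eight a month is 8/30.4 = 26% of daily use, and the subgroup cut, "the dose of moxibustion: ≥3 sessions/wk vs <3 sessions/wk", is about 13 a month. Daily use is only suggested and patients may adjust it, so a lenient floor for poor compliance is consistent with the pragmatic design. The subgroup cut serves another purpose, and a patient can be above one and below the other without contradiction.
- *Early stoppers pass as compliant on a yearly average.* Daily use for 4 months and then none does average 4 × 30/12 = 10 a month. But no section mentions a yearly average, and the rule is most naturally read month by month, where that patient fails from month 5.
- *The Discussion fixes a feasibility decision rule.* The remark stands in a limitations paragraph and runs one way only. It says what poor compliance would show, and does not say that a low proportion proves feasibility.
- *A figure for how many patients would lapse at least once.* This needs a monthly lapse risk, which the article does not give, and independence between months, which is implausible for adherence. None is offered here.

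**Conclusion.** The point holds in this form: compliance is defined per month, reported as one proportion, and assigned to the per-protocol population. Followed as written, the measure can omit patients who stopped and understate poor compliance, for an outcome that the authors use to speak about one-year feasibility.

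The understatement is s(1 − p). Over the illustrative range of s from 10% to 40% and p from 0% to 20%, it is 8 to 40 percentage points. Those values are assumptions, and the true size depends on how many patients stop and how the per-protocol population is defined. The direction does not depend on them. The threshold of 8 is not in question, and neither is the intention-to-treat analysis of the primary outcomes. The change is worth making because it is cheap and answers the study's own question more directly.

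**What to change.** 1. In 2.12, exempt compliance from the per-protocol rule. Analyse it in all patients who entered the moxibustion group, and count those who stop or withdraw as below the threshold from then on.
2. In 2.6.2, keep the 8-session threshold, apply it to each month, and report the proportion below it month by month.
3. Base the feasibility statement in the Discussion on persistence at the end of the year: the proportion of all who entered the group with at least 8 sessions in each of months 10, 11 and 12.
4. In 2.8, confirm that compliance is also recorded at the month 6 and month 12 visits. Without the month 12 record, the persistence measure cannot be computed.

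The cost is wording, a small extra analysis and, if not already planned, one more item at two existing visits. No dose or clinical rule changes. The reported compliance may look less favourable.
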